## Methods

### Study design and setting

This protocol follows the CONSORT (Consolidated Standards of Reporting Trials) statement guidelines for cluster trials.^28^

This study is a multicentre, parallel group, pragmatic cluster RCT (2015-18).^29^ It is nested within a larger ongoing Bridging the Age Gap cohort study (2012-18)^21^ (figure 1) which is currently recruiting from 53 breast units within in the UK (observational cohort study of current UK management of older women with early breast cancer).

### The RCT study

The intervention comprises implementation of a package of two DESIs for the PET versus surgery/AET, or chemotherapy versus no chemotherapy decisions. Each DESI includes an online algorithm for treatment outcomes, and two PtDAs—a booklet and a brief option grid.^26 27^ Each DESI is a complex intervention, including training for the clinician (breast surgeon, medical oncologist, breast care nurses) on the use of the algorithm (surgeons and medical oncologists only) or PtDAs, and the clinician and patient decide which, if any, of these elements they wish to use to assist the decision-making process, the intention being for the intervention to be used as part of everyday clinical practice/pathway within the intervention sites.

Each online algorithm includes functionality to adjust outcome prediction according to patient age, comorbidity, frailty, tumour stage and ER status and which gives outputs of 2 and 5-year overall and breast cancer specific survival. The algorithms were developed in the earlier phase of the Age Gap study^25^ and were designed to guide clinicians and their patients in the treatment of:frailer older women with ER-positive breast cancer to optimise treatment with either PET or surgery/AET;fitter older women who have already had primary surgery and been found to have high-risk cancer characteristics (eg, ER-negative, HER2-positive or node-positive breast cancer) to optimise treatment with either adjuvant chemotherapy or no adjuvant chemotherapy (note the term chemotherapy includes chemotherapy +/− trastuzumab if appropriate).

The algorithm is based on a computer model of predicted outcomes and variance caused by patient and disease parameters. Unlike existing web-based algorithms for cancer treatment (Adjuvant!OnLine^19^ or PREDICT^20^) which do not have the facility to specify frailty or comorbidity in detail (or at all), the Age Gap algorithm permits these factors to be taken into account. The Age Gap tool has been optimised for accuracy in this age group and has been based on analysis of data from over 20 000 UK women over the age of 70 derived from cancer registry data. The algorithm has built-in educational materials (including several online presentations, data sources, FAQs and an animated educational video). The online algorithm is designed to be used by clinicians to guide treatment decision making and its outputs can be printed off in a patient-facing format that could be used in personalised patient counselling. The report provides specific survival estimates for each treatment option for an individual woman based on her personal and cancer characteristics. This works in much the same way as the printouts from Adjuvant!Online^19^ or PREDICT^20^ but in this case developed for the PET versus surgery/AET decision and with more detailed data entry relating to the woman's age and fitness level.

Two PtDAs (PET vs surgery/AET^26^ and chemotherapy vs no chemotherapy^27^) have been developed during the earlier phase of the study.^22–24^ The PtDAs comprise an option grid^30^ and a booklet for each decision. The option grid is a one-page evidence-based summary of the treatment options alongside patients’ frequently asked questions, helping patients to differentiate the key features, risks and benefits of treatment options in relation to their personal values and preferences. The option grid has been designed to be sufficiently brief for use in clinical encounters and accessible enough to support a better dialogue between patients and their clinical team.^30^ The booklet provides information about both options including diagrams, side effects and potential risks and benefits. It also includes a section to guide deliberation and encourage the patients to clarify their preferences based around identifying ‘what is most important to them.’^16^

### Eligibility criteria

#### Inclusion criteria

female;aged over 70 years at the time of diagnosis of cancer;primary operable (tumour, node, metastasis (TNM) categories V7: T1, T2, T3, N0, N1, M0), ER-positive invasive breast cancer (core biopsy or diagnostic incision biopsy);ability to give informed consent and to read English.

#### Exclusion criteria

disease unsuitable for surgery, for example, inoperable, locally recurrent or metastatic disease;previous invasive breast cancer within the last 5 years;non-English speakers.

### Data collection and outcomes

#### Primary outcome measure

The primary outcome measure for the RCT is global health status/QoL score (questions 29+30 only of The European Organization for Research and Treatment of Cancer QLQ-C30 Reference Manual) (EORTC QLQ-C30).^31^ This primary endpoint was stipulated by the funder of the study with the justification being that the EORTC QLQ-C30 is internationally recognised and well-validated QoL measure (as opposed to our original primary endpoint of decision quality). This was measured at 6 weeks and 6 months postdiagnosis/consent.

An independent data monitoring committee (DMC) comprising three experienced academic clinicians oversees the study and monitors trial conduct and safety and potential harm and has access to all study data; the role being to provide recommendations for trial changes (or closure). Data collection is being undertaken by trained clinical staff within each of the participating sites. The study data manager and study monitor also undertake regular site visits to outline the study protocol, ensure protocol adherence and monitor data collection and completeness. Data collection for the study includes detailed information about the patients and their cancer at the time of diagnosis: age, comorbidity (Charlson comorbidity index,^32^ frailty—The Barthel Index (ADL, activities of daily living)^33^ and instrumental activities of daily living scores (IADL)^34^), cognitive status (Mini-Mental State Examination),^35^ baseline QoL (EORTC QLQ C30,^31^ EORTC breast cancer-specific QoL questionnaire (QLQ-BR23),^36^ EORTC QoL questionnaire module for older people with cancer (QLQ-ELD14),^37^ EuroQol Group EQ-5D^38^), tumour stage, grade and receptor status. Treatment details are recorded including the type of surgery to the breast and axilla, use of adjuvant therapies (chemotherapy, radiotherapy, trastuzumab and hormonal therapies), including doses and adverse effects recorded using the Common Terminology Criteria for Adverse Events grading system. Follow-up is at baseline, 6 weeks, and 6, 12, 18 and 24 months after diagnosis/consent. Cancer outcomes, QoL and adverse events are recorded at each visit and in the longer term, women are asked to sign a consent form to permit the trial to collect their Cancer Registry data which will be collected 5 and 10 years following diagnosis and consent to the study. These data will permit us to look at whether using the DESIs alters patterns of treatment decision making between control and intervention sites and whether these impact on long-term outcomes. As such this is a uniquely detailed evaluation of such DESIs.

In addition, specific questionnaires relating to patient choice and decision making will be administered. These will apply to all women offered a choice of either PET and surgery/AET or chemotherapy versus no chemotherapy and are administered in relation to the time of their treatment choice. Secondary outcome measures here include decision regret (Decision Regret Scale,^39^ shared decision making (CollaboRATE^40^), patient anxiety (Spielberger short-form state scale of the State-Trait Anxiety Inventory,^41^ knowledge and preference (knowledge, readiness to decide and preference measure^42 43^), illness perceptions (Brief Illness Perceptions Questionnaire^44^) and Coping (brief COPE, Coping Orientation to Problems Experienced)^45^). Original data collected are entered and kept on file within each of the study sites. These data are entered electronically and stored securely onto password-protected databases within local databases and the main trial office. All records that contain names or other personal identifiers, such as locator forms and informed consent forms, are stored separately from study records identified by code number. Only the study steering and DMC have access to the full trial data set. Errors, discrepancies or missing data are captured by the computer programme and the study data manager checks and subsequently follows this up with participating sites.

The timescales for each of these are shown in table 1.

**Table 1 d35e986:** Questionnaire schedule

Standard age gap questionnaires	Baseline	6 weeks	6 months	12 months	18/24 months	Long term
IADL	*					
ADL	*					
MMSE	*					
ECOG performance status	*					
Subjective global assessment	*					
Comorbidity	*					
EQ5D	*	*	*	*	*	
QoL (EORTC-QLQ C30, QLQ-BR23 and QLQ-ELD14)	*	*	*	*	*	
Decision quality	*	*				
RECIST if PET	*	*	*	*	*	
Registry data access						*
Tissue access	*					*
Tumour details	*					
Treatment details	*	*	*	*	*	
Adverse events	*	*	*	*	*

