**Trial registration number:**

European Union Drug Regulating Authorities Clinical Trials (EudraCT) number 2015-004220-61;Pre-results. Sponsor's Protocol Code Number Sheffield Teaching Hospitals STH17086. ISRCTN 32447*.

Strengths and limitations of this studyThe two evidence-based decision support interventions (DESIs) for women over 70 years diagnosed with breast cancer who are offered a choice of primary endocrine therapy or surgery (plus adjuvant endocrine therapy, hereafter termed surgery/AET, antioestrogen therapy) or chemotherapy versus no chemotherapy are, to the best of our knowledge, the first of its kind worldwide.The web-based clinical outcomes management algorithm is the first of its kind and allows patient age, comorbidities, frailty and cancer characteristics to be considered in predicting breast cancer survival and cancer outcomes.A limitation of the trial will potentially be selection bias from recruitment and poor uptake/utilisation of the DESIs at intervention sites.A second limitation may be an inability to demonstrate a benefit in terms of cancer survival rates without at least 5–10 years follow-up or an overall survival advantage due to the competing causes of death in this age group.

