**Table d35e1183:** 

New for DESI study **(if offered choice of either pet or surgery/AET, or chemotherapy/no chemotherapy)**	Baseline **(after consent for PET or surgery) (AET or after consultation for chemo/no chemo, as applicable)**	6 weeks after relevant treatment choice	6 months after relevant treatment choice			
Spielberger anxiety		*	*			
Collaborate	*					
Decision regret		*	*			
Knowledge readiness to decide and preference measures	*					
Brief IPQ		*	*			
Brief COPE		*	*			
Process evaluation (if taking part in process evaluation)						
Process evaluation questionnaire		*				

*indicated that these data are collected at this time point.

ADL, activities of daily living; AET, antioestrogen therapy; COPE, Coping Orientation to Problems Experienced; DESI, decision support intervention; ECOG, Eastern Cooperative Oncology Group; IADL, instrumental activities of daily living; IPQ, Illness Perception Questionnaire; MMSE, Mini-Mental State Examination; PET, primary endocrine therapy; QoL, quality of life; RECIST, Response Evaluation Criteria In Solid Tumors.

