### Randomisation

Randomisation is at breast unit level, stratified by high and low PET and chemotherapy rates. It was therefore not possible to blind the investigators or the study sites to the allocation of participants. Data for this stratification have been derived from the wider cohort study which has collected data on treatment rates for both PET versus surgery/AET and chemotherapy versus no chemotherapy.

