### Recruitment

Potentially eligible women are identified by clinicians (breast surgeons, medical oncologists and specialist breast nurses) and research nursing staff within multidisciplinary teams of the study sites. Study packs are being given to eligible patients either following their clinical consultation where either PET or surgery/AET options or chemotherapy versus no chemotherapy options are discussed. Monthly study newsletters are sent to all participating sites to provide feedback to staff in order to maintain interest and recruitment to the study. Any modifications to the original study protocol will be discussed with the data monitoring and ethics committee and approvals sought from the funder and the ethics committee. Recruitment for the trial has now commenced and 750 women have been recruited over the 53 participating sites.

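### The added decision questionnaires go only to women offered a choice, a condition set after unblinded cluster allocation, so the arms can differ in case mix on these secondary outcomes

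*Protocol article*

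**What the plan says.** All places are in the protocol article.

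- **Who completes the decision questionnaires.** Data collection and outcomes restricts them to women given one of the two choices: "These will apply to all women offered a choice of either PET and surgery/AET or chemotherapy versus no chemotherapy". The schedule for the instruments new to the DESI study repeats the condition: "if offered choice of either pet or surgery/AET, or chemotherapy/no chemotherapy".
- **Allocation and blinding.** Randomisation is by breast unit, stratified by PET and chemotherapy rates. Of blinding it says: "It was therefore not possible to blind the investigators or the study sites to the allocation of participants".
- **What differs between arms before recruitment.** Under Intervention arm, both groups of units attended a training event. Only intervention units were also trained in shared decision making and in using the DESIs.
- **Recruitment.** "Potentially eligible women are identified by clinicians (breast surgeons, medical oncologists and specialist breast nurses) and research nursing staff". The only time point named for the packs is after the options have been discussed: "Study packs are being given to eligible patients either following their clinical consultation".
- **Eligibility.** The criteria are clinical, plus consent and language. Being offered a choice is not among them.
- **Protection.** The strengths and limitations list concedes: "A limitation of the trial will potentially be selection bias from recruitment". Data analysis plans intention-to-treat comparisons, with covariate adjustment if the arms are found to differ at baseline.
- **Outside the condition.** Table 1 puts EORTC quality of life, which includes the primary outcome, and a decision quality item on the standard schedule for all women.

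**The concern.** In a cluster trial, randomisation makes the populations served by the units comparable. It does not make a subset comparable if membership is decided later by people who know the allocation. Being offered a choice is such a subset. It is settled in the consultation, by clinicians who in one arm only have been trained to share decisions and given tools for exactly these two decisions. If that training widens, narrows or redirects the offer, the women who answer the questionnaires differ between arms for reasons unrelated to any benefit of the DESIs.

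The outcomes at stake carry the hypotheses on shared decision making and regret, and on illness representations and coping. A difference in regret or coping could then reflect case mix, in either direction.

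The primary outcome is exposed by a different and weaker route. Women are identified by unblinded site staff and receive packs after the options consultation, so who enrols could depend on arm. That the site staff also hand over the packs is inferred from Randomisation and Recruitment; the article does not say so outright.

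**Working it through.** **1. The plan's own figure.** Inputs from Sample size calculation: difference 7, SD 21, two-sided 5%, power 90%, ICC 0.03, 10 women per cluster, 20% loss.

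- Per arm: 2 × (1.960 + 1.282)² × 21² / 7² = 189.1, so 190 (reproduces).
- Design effect: 1 + 9 × 0.03 = 1.27, given as 1.3. 380 × 1.27 = 483 and 380 × 1.3 = 494, taken up to 50 × 10 = 500.
- Loss: 10 / 0.8 = 12.5, so 13 per cluster and 650 in total.

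This figure is sound and does not bear on the concern. It supplies 250 analysed per arm and hence a standard error: √(2 × 1.27 / 250) = 0.101 SD, or 21 × 0.101 = 2.12 points.

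**2. Order of events.** Units allocated → intervention units trained → women seen and options discussed → choice offered or not → pack given → decision questionnaires given if a choice was offered. The filter comes after allocation and after the intervention has begun to act.

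**3. Can the planned adjustment repair it?** In the schedule, regret, anxiety, Brief IPQ and Brief COPE are first measured 6 weeks after the treatment choice. CollaboRATE and knowledge/preference are measured once, at a baseline that itself follows consent or the consultation. None has a pre-intervention value. Adjustment is also triggered only by observed imbalance. Intention-to-treat keeps a woman in her unit's arm but does not restore those who never entered the denominator.

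**4. Possible size for the restricted outcomes.** The article gives no offer rates, so everything here is assumed: no true effect; choice offered to the frailest fraction *p* of women; correlation ρ of 0.2 to 0.5 between frailty and outcome; 250 analysed per arm; design effect 1.27; no covariate adjustment.

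Mean frailty among those offered: m(p) = φ(z₁₋ₚ) / p, giving m(0.30) = 1.159, m(0.40) = 0.966, m(0.45) = 0.880, m(0.50) = 0.798.

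Spurious difference: d = ρ × [m(control) − m(intervention)].

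False-positive rate: P(|Z + d/0.101| > 1.96).

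| Offered, control v intervention | d (SD) | False-positive rate |
|---|---|---|
| equal and equally selective | 0 | 5% |
| 40% v 45% | 0.02–0.04 | 5–7% |
| 40% v 50% | 0.03–0.08 | 6–13% |
| 30% v 50% | 0.07–0.18 | 11–43% |

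On a scale with SD 21, the last row is 1.5 to 3.8 points. SD 21 belongs to the quality-of-life scale, so the points are only a guide for the decision measures. With fewer than 250 analysed per arm, d is unchanged and the false-positive rate is lower.

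**5. Possible size for the primary outcome through recruitment.** If case mix shifted the unadjusted mean by 1, 2 or 3 points (assumed), d/SE is 0.47, 0.94 or 1.42, and the false-positive rate is about 8%, 16% or 29%. Adjustment for baseline quality of life would reduce this where that form predates the consultation.

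**The case against.** Several points on the other side stand.

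- **No difference is shown.** The article does not say that the DESIs change who is offered a choice. It expects changes in treatment rates, which is not the same thing. A reader might infer that the arms do compare different kinds of women; the text supports only that they can.
- **Not every outcome is restricted.** A reader might infer that all decision outcomes, or the primary outcome, come only from women offered a choice. Table 1 places decision quality and EORTC quality of life on the standard schedule without that condition.
- **There is some protection.** A reader might infer that nothing is planned against selection. Stratification by earlier PET and chemotherapy rates, collection of age, comorbidity and function, and conditional baseline adjustment all help. They are partial: stratification balances units beforehand, and adjustment depends on imbalance being noticed.
- **The restriction fits one hypothesis.** The hypothesis on decision quality and regret concerns women facing a choice, so the restricted set is partly a choice of estimand. The hypothesis on illness representations and coping is worded for women at the sites generally, and the criticism is stronger there.
- **Some detail may be elsewhere.** Screening logs and a working definition of the offer may stand in the full protocol. The condition itself is stated here, however, and a better definition would not move it before allocation.
- **Measuring everyone has limits.** Regret has no anchor in a woman given no choice. The chemotherapy group is identified only after surgery, so data at diagnosis cannot define it.

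**Conclusion.** The concern holds for the secondary outcomes new to the DESI study: regret, CollaboRATE, anxiety, knowledge/preference, Brief IPQ and Brief COPE. Their denominator forms after unblinded cluster allocation, at the step the intervention is meant to influence, and neither intention-to-treat nor adjustment conditional on observed imbalance repairs it. The primary outcome and the standard decision quality item are exposed only to possible recruitment bias from enrolment after the consultation.

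The documents establish a mechanism, not an observed imbalance. The size cannot be derived from them. It is nil if offers are equally frequent and equally selective, close to nominal for a small difference in offer rate, and material only for larger differences combined with a strong link between selection and outcome. All figures rest on the assumed rates, correlations and numbers analysed. The point deserves action because the remedy is cheap and, without it, a difference on these outcomes could not be separated from case mix.

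**What to change.** 1. Record for every enrolled woman whether a choice was offered. Report that proportion, and the characteristics of those offered a choice, by arm.
2. For the PET versus surgery decision, define a decision-eligible analysis set by a fixed rule on data collected at diagnosis (ER status, stage, age, Charlson, ADL/IADL), identical in both arms. From now on, give every woman who meets it the questionnaires that make sense without an offered choice (CollaboRATE, anxiety, Brief IPQ, Brief COPE, knowledge), timed from the treatment decision. The rule defines who is analysed and says nothing on who should be offered which treatment.
3. Keep the offered-a-choice comparison for regret and for the chemotherapy decision. Adjust it for the same prespecified covariates whether or not imbalance is seen, and label it supportive and non-randomised.
4. Flag baseline quality-of-life forms completed after the options consultation.

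**Cost.** Protocol wording, a site instruction and some additional questionnaires. Recruitment reports 750 women already enrolled against a target of 650, so item 2 may reach few women. Those already recruited without a choice lack these outcomes and need a flagged sensitivity analysis. Item 3 needs only covariates already collected, and so does item 1 wherever the offer can be established from records.

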**Table d35e1183:** 

New for DESI study **(if offered choice of either pet or surgery/AET, or chemotherapy/no chemotherapy)**	Baseline **(after consent for PET or surgery) (AET or after consultation for chemo/no chemo, as applicable)**	6 weeks after relevant treatment choice	6 months after relevant treatment choice			
Spielberger anxiety		*	*			
Collaborate	*					
Decision regret		*	*			
Knowledge readiness to decide and preference measures	*					
Brief IPQ		*	*			
Brief COPE		*	*			
Process evaluation (if taking part in process evaluation)						
Process evaluation questionnaire		*				

*indicated that these data are collected at this time point.

ADL, activities of daily living; AET, antioestrogen therapy; COPE, Coping Orientation to Problems Experienced; DESI, decision support intervention; ECOG, Eastern Cooperative Oncology Group; IADL, instrumental activities of daily living; IPQ, Illness Perception Questionnaire; MMSE, Mini-Mental State Examination; PET, primary endocrine therapy; QoL, quality of life; RECIST, Response Evaluation Criteria In Solid Tumors.

